# PRObiotics and SYNbiotics to improve gut health and growth in infants in western Kenya (PROSYNK Trial): study protocol for a 4-arm, open-label, randomised, controlled trial

**DOI:** 10.1186/s13063-022-06211-1

**Published:** 2022-04-11

**Keywords:** Environmental enteric dysfunction, Probiotic, Synbiotic, Inflammation, Gut health, Nutrition, Growth

## Abstract

**Background:**

Malnutrition amongst under-fives remains common in resource-poor countries and is resistant to current interventions. New opportunities have emerged to target “environmental enteric dysfunction” (EED) that refers to the abnormal gut structure and function that results from colonisation of the gut with pathogenic microbes and compromises nutrition and growth in early life. Although the gut microbiome may provide a defence against ingested gut pathogens through colonisation resistance, its development is adversely affected by multiple environmental factors. Dietary supplements of pro- or synbiotics may build the resilience of the gut microbiome against these environmental factors and boost colonisation resistance. We aim to assess whether dietary supplementation of newborns in rural Kenya with pro/synbiotics prevents or ameliorates EED and improves growth.

**Methods:**

Six hundred newborns less than 4 days old will be recruited from Homa Bay County Teaching and Referral Hospital, western Kenya. Newborns will be randomly allocated, stratified by HIV exposure, in a 1:1:1:1 ratio to one of 4 study arms to receive either of two synbiotics, a probiotic or no supplement. Supplements will be given daily for 10 days and then weekly until 6 months of age. Participants will be followed until the age of 2 years. The primary outcome is systemic inflammation at 6 months assessed by plasma alpha-1-acid glycoprotein. Secondary outcomes include biomarkers of gut health and growth, anthropometric indices, morbidity and mortality.

**Discussion:**

As dietary supplements with pro- or synbiotics may improve gut health and can be administered in early life, our findings may inform the package of interventions to prevent malnutrition and improve growth in Africa and similar low-resource settings.

**Trial registration:**

Pan African Clinical Trials Registry, Trial number: PACTR202003893276712. Date: 02/03/2020 https://pactr.samrc.ac.za/TrialDisplay.aspx?TrialID=9798

**Supplementary Information:**

The online version contains supplementary material available at 10.1186/s13063-022-06211-1.

## Administrative information

Note: the numbers in curly brackets in this protocol refer to SPIRIT checklist item numbers. The order of the items has been modified to group similar items (see http://www.equator-network.org/reporting-guidelines/spirit-2013-statement-defining-standard-protocol-items-for-clinical-trials/).

## Introduction

### Background and rationale {6a}

In 2020, more than 1 in 5 under-fives (149.2 million worldwide) were stunted and wasting affected 6.7% of children (45.4 million), of whom 13.6 million had severe wasting [1]. Chronic malnutrition, evidenced by stunting, is associated with significantly impaired cognitive development and the growth and development of other organs [2–4]. An aggregate measure of undernutrition was estimated to account for up to 3.1 m under-five deaths (45% of all child deaths) in 2011 [5].

Current interventions, including exclusive breastfeeding (EBF), have limited impact on growth as achieving 90% coverage with the ten best evidence-based nutrition-specific interventions would reduce stunting by only 20% [6]. In the recent water, sanitation and handwashing (WASH) Benefits studies in Bangladesh and Kenya, children who received food supplements with or without other interventions had improved linear growth but the benefit was limited: in Bangladesh, the mean difference in length-for-age *Z* score at age 2 years was 0.25 (95% confidence interval (CI) 0·15–0.36) in children receiving a nutritional supplement [7] and in Kenya 0.16 [0·05–0·27] in children in the combined water, sanitation, handwashing and nutrition group [8]. Although EBF is universally accepted as the optimal mode of feeding young infants [9], research studies have not found that EBF improves infant growth [10–14].

Targeting “environmental enteric dysfunction” (EED) may offer new opportunities. EED refers to the abnormal gut structure and function that is universal in people living with poor sanitation and hygiene with onset as early as age 12 weeks despite EBF [15]. The gut pathology is characterised by villous atrophy, chronic inflammation and a “leaky” mucosa. The consequences are reduced absorption of nutrients, increased systemic inflammation and impaired immune responses to oral vaccines [15, 16].

Several recent studies have confirmed that, in the context of poor nutrition and in addition to diarrhoeal episodes, frequent sub-clinical enteric infection with organisms that damage the intestinal mucosa results in EED and contributes to systemic inflammation that directly impairs linear growth through decreased production of growth hormones [17–20]. In the MAL-ED study, gut inflammation was most closely associated with poor weight gain whilst systemic inflammation correlated closely with stunting [19]. EED is a sub-clinical condition manifest only by growth failure. Although intestinal biopsy to directly evaluate enteropathy is not feasible or justified in community-based studies [21], the association of multiple biomarkers reflecting the different pathologies of EED and its consequences with growth faltering in children have been assessed [19, 21–23].

### Justification for the study

The gut microbiome is critical for the development of the gut, brain and other organs, mucosal and systemic immunity and protection against gut infection through colonisation resistance [24–27]. In healthy, breastfed infants, bifidobacteria flourish and become abundant. Bifidobacteria facilitate further gut colonisation by a diverse range of anaerobes by “cross-feeding” through hydrolysis of complex carbohydrates and the production of organic acids. Some strains of lactobacilli and bifidobacteria have direct immune-modulatory, anti-inflammatory and anti-pathogen effects, the latter partly mediated through acidifying the intestinal lumen through increased production of organic acids [24, 28, 29]. As key “pioneer” organisms creating the right environment in the gut for colonisation with a broad range of healthy anaerobic bacteria, lactobacilli and bifidobacteria may have long-term benefits that persist into adult life reducing the risk of common metabolic diseases as well as improved long-term gut health and immunity [25].

Several common environmental factors may either delay or disturb the development of the gut microbiome resulting in dysbiosis. These include Caesarean section delivery, hospital admission, maternal/infant antibiotics, poor hygiene and sanitation, parasite infection and faulty feeding practices [29–34]. Additionally, maturity at birth has been found to affect microbiota development with those extremely premature infants at risk of delayed microbiota development [35]. Several studies have reported delayed maturation of the gut microbiome and a deficiency of *Bifidobacterium* in children with malnutrition [36].

Administration of pro- or synbiotics may be a feasible, safe and effective means of building the resilience of the developing gut microbiome against environmental factors in early life. Probiotics are live, non-pathogenic microorganisms that, when administered in adequate amounts, confer a health benefit on the host [37]. Commonly used probiotics are strains of lactobacilli and bifidobacteria. Prebiotics are defined as substrates that are selectively utilised by host microorganisms conferring a health benefit [38]. Prebiotics are present in breast milk as human milk oligosaccharides. Oligosaccharides are commonly used prebiotics and increase bifidobacteria and related taxa [38]. Synbiotics combine prebiotics with probiotics.

The feasibility of administering pro- or synbiotics, including during exclusive breast feeding, was confirmed in a large trial in poor rural communities in India. A synbiotic given for 7 days in approximately 2000 newborns (and 2000 controls), nearly all of whom were breastfed, significantly reduced sepsis, pneumonia and skin infections [39]. A previous search of several registries did not identify any on-going studies evaluating prebiotics, probiotics, or synbiotics in preventing of EED or malnutrition.

### Objectives {7}

#### Goal

This project addresses a pragmatic, public health question: in infants exposed to high levels of faecal-oral pathogen transmission, does the administration of pro/synbiotics early in life improve gut health and growth?

#### Primary objective

To determine whether dietary supplementation with a pro- or synbiotic of newborns during the first 0–5 months of life reduces systemic inflammation at age 6 months assessed by plasma alpha-1-acid glycoprotein (AGP).

#### Secondary objectives

To determine:
Whether pro/synbiotic administration improves biomarkers of intestinal inflammation and leakiness, reduces stool pH and improves levels of growth hormones at 6 weeks and 3, 6 and 12 monthsWhether pro/synbiotic administration reduces episodes of illness (e.g. diarrhoea, respiratory and skin infections)Whether pro/synbiotic administration improves gain in weight, length and head size up to age 2 yearsFeeding and WASH practices and environmental factors that likely influence the development of the gut microbiome

### Trial design {8}

We will undertake an exploratory, individually randomised, 4-arm, parallel-group, open-label, controlled study of a probiotic and two synbiotics in infants 0–5 months of age in western Kenya.

## Methods: participants, interventions and outcomes

### Study setting {9}

The project will be conducted in rural communities in Homa Bay County in western Kenya. In Nyando Division, a largely rural region in previous Nyanza Province, surveys in 2007–2009 of > 1000 children aged 6–35 months reported that 5% of children were wasted (WHZ < − 2 *z* score) and 28% were stunted (HAZ < − 2 *z* score) [40]. Surveys undertaken in 2014/15 of 858 under-fives in 10 villages (1800 households) reported mean (SD) WHZ score was − 0.12 (± 1.1) with 4.8% children wasted and a mean (SD) HAZ score was − 1.2 (± 1.2) with 23.5% stunted [41]. The WASH Benefits study undertaken in rural villages in the western region reported that in control children with a median age of 2.05 years (IQR 1.93–2.16), mean length-for-age *z* score was − 1.54, 31.5% of children were stunted, 9.3% had severe stunting, 9.6% were underweight and 1.4% were wasted [8]. Around 1 in 4 caregivers reported diarrhoea in their children in the past 7 days.

The project will be based in the Homa Bay County Teaching and Referral Hospital, a 280-bed government facility. The hospital has between 250 and 300 deliveries/month with satellite ante-natal care (ANC) clinics in Homa Bay County. Additional back-up sites in the County may also be included should recruitment be lower than expected.

### Eligibility criteria {10}

#### Inclusion criteria

Singleton newborn aged 1–3 daysBirthweight (BW) or current weight (if BW not known) ≥ 2000 gWell infant who is breastfed and has taken at least one breast feed wellLives within the catchment area of the research centre at Homa Bay HospitalInformed consent secured from mother/carerInfants of HIV-positive women without known immunosuppression will be eligible to join the study.

#### Exclusion criteria

Multiple pregnancy (e.g. twin/triplets)Infant aged 4 days or olderSuspicion or presence of any acute illness (e.g. fever; receiving treatment with antibiotics)Congenital abnormality that might be life-threatening or impair growthInfant with potential contraindication to pro/synbiotics (e.g. suspected immune suppression; cardiac abnormality)Mother unlikely to stay in study area for the duration of the studyAny health staff or study staff concerns regarding safety to participate in the trial

### Who will take informed consent? {26a}

Written, informed consent will be obtained in the local vernacular language by Community Interviewers who will be part of the study team. The consent process shall be initiated when women attend ANC in the last trimester of pregnancy or for delivery. Mother/carers whose newborns may meet the eligibility criteria will have the study explained to them by a member of the study team and provided with an information sheet in an appropriate language. If the newborn meets the eligibility criteria, the consent process will follow, with a written consent form provided. A copy of the informed consent document will be given to the participant for their records unless they state that they do not wish to have a copy.

For illiterate mothers/carers, an independent witness will be present during the informed consent process and will sign the consent form, whilst the participant will be asked to indicate consent by thumbprint. The participant may withdraw consent at any time throughout the course of the study, and this will be made clear in the informed consent process.

All mothers/carers will be informed that there is no requirement to join the study and that standard medical care will remain the same regardless of study enrolment.

The mother/carer will be given the option to take the patient information sheet and consent statement home and encouraged to ensure that the child’s father and other significant family members are aware of the study and agreeable for the child to participate. The child’s father may sign the study consent form as the adult providing consent for baby.

### Additional consent provisions for collection and use of participant data and biological specimens {26b}

A request for informed consent to donate any remaining samples for future research, including possible shipment to laboratories at the Liverpool School of Tropical Medicine, Liverpool, UK, for analyses not available in Kenya, will be included in the consent form. This will allow the study to save and store long term any spare stool and blood samples for possible future analyses relevant to gut health and nutrition in early life. These may include nutrient assays in blood (e.g. iron), detection of the probiotic organisms and specific enteropathogens in stool and microbiota analysis.

## Interventions

### Explanation for the choice of comparators {6b}

The selection of probiotics was based on their previous safe use in infants and manufactured according to Good Manufacturing Practice (GMP) and with good shelf life at ambient temperature. The safety of the Lab4b bacteria in newborns was confirmed in a UK study [42]. Lactobacilli and bifidobacteria were administered routinely in about 70% of preterm infants in Germany [43]. A survey reported that Labinic was used routinely in 7 UK neonatal units [44] and several treatment protocols and patient information sheets are available for preterm infants (e.g. http://swneonatalnetwork.co.uk/media/105774/swnn-guideline-probiotics.pdf). Clinical experience of this product in highly vulnerable preterm infants has not raised concerns regarding safety ([name]; personal communication). The sensitivity of the probiotic strains to antibiotics used for sick infants in Kenya was confirmed (Additional file 1).

The combination of the probiotics with a prebiotic was based on the reduction in neonatal sepsis when a synbiotic (*Lactobacillus plantarum* ATCC strain 202195 in combination with fructooligosaccharide (FOS)) was administered to newborns in Odisha, India [39]. A neonatal study reported that the BENEO Orafti Synergy 1 prebiotic added to infant formula resulted in comparable *Bifidobacterium* levels in stools compared to breastfed infants and enhanced when compared with GOS:FOS 90:10 supplemented infant formula [45].

The effects of the administration of a probiotic alone versus a synbiotic and the different synbiotic preparations will be assessed by comparing outcomes in the following four study arms.

### Intervention description {11a}

Participants will be randomly allocated to one of 4 study arms:
Arm 1: Labinic synbiotic daily for 10 days and then weekly to age 6 monthsArm 2: Lab4b probiotic daily for 10 days and then weekly to age 6 monthsArm 3: Lab4b synbiotic daily for 10 days and then weekly to age 6 monthsArm 4: Control group; no dietary supplement

Infants in the control arm will receive the same home visits as those receiving a pro/synbiotic.

#### Details of pro/synbiotics

Labinic synbiotic: prebiotic (BENEO Orafti Synergy1; 50% oligofructose:50% FOS; 200 mg) + 3 live bacteria: *Lactobacillus acidophilus* NCFM, *Bifidobacterium infantis* Bi-26 and *Bifidobacterium bifidum* Bb-06; total of 5 billion organisms/day (https://biofloratech.com/EU_page_Labinic_Drops.html).Lab4b probiotic: 4 live bacteria: *Lactobacillus salivarius* CUL61, *Lactobacillus paracasei* CUL08, *Bifidobacterium animalis subspecies lactis* CUL34 and *Bifidobacterium bifidum* CUL20; total of 10^10^ organisms/day (https://www.lab4probiotics.co.uk/).Lab4b synbiotic: prebiotic (long-chain FOS 150 mg/day) + Lab4b probiotic.

All three supplements will be presented as powder inside capsules with one dose/capsule. In this open-label study, the colour of the capsules differs for each preparation to facilitate correct administration. The contents of the capsule can be sprinkled directly into the infant’s open mouth before feeding or mixed in a clean container with sterile water. The administration will be repeated once if the infant vomits within 30 min. All administration of supplements will be supervised by a member of the research team.

In infants taking antibiotics, including HIV-exposed infants taking co-trimoxazole daily from age 4–6 weeks, the supplements will be administered at least 4 h before/after the antibiotic or between doses to minimise the effect of the antibiotic on the microbes. We aim to start the interventions in infants within the first 3 days of birth to limit potential competition from other gut organisms against the probiotics.

Although the dietary supplements are stable at ambient temperatures below 25 °C for up to 2 years, viability at higher temperatures has not been assessed. Therefore, a cold chain was maintained during shipment of the supplements with storage at 5 °C ± 3 °C in Kenya and transfer to participants’ home in a cold box. Quantitative counts of the probiotics will be done at intervals during the study to confirm viability.

### Criteria for discontinuing or modifying allocated interventions {11b}

The dietary supplements will be discontinued in any infants in whom there is a concern by a member of the study team or a health professional that they may be causing harm. Mothers/carers can withdraw their infant from the study at any time should they have any similar concerns. Administration of the pro/synbiotics will be discontinued if there are concerns regarding loss of viability.

### Strategies to improve adherence to interventions {11c}

Mothers/carers will be assisted in administering the dietary supplements to their infants. All administrations will be done under the supervision of study staff who will record adherence. Where feasible, study participants will be reminded about follow-up visits through mobile phone contact. Home visits to both intervention and control infants will include advice regarding healthy feeding and childcare practices.

### Relevant concomitant care permitted or prohibited during the trial {11d}

All participants will be offered routine care according to local and national policies. This includes all childhood vaccinations during infancy and advice regarding the importance of exclusive breast feeding, complementary feeding from age 6 months and sleeping under an insecticide-treated bed net. The study team will re-enforce these positive health messages where appropriate. All routine medications used for the treatment of childhood illnesses is permitted and concomitant medications taken during the study will be recorded with indications and dates of administration. No medications are prohibited. Study staff will facilitate referral to health services for infants who are unwell during scheduled and unscheduled study visits.

### Provisions for post-trial care {30}

The study is not able to fund post-study care or implementation of pro/synbiotics as policy. However, the investigators will ensure that policymakers (e.g. WHO) and funders (e.g. CIFF) are informed early of germane research findings.

### Outcomes {12}

#### Primary outcome

The primary outcome will be raised plasma AGP concentration (> 1 g/L) at age 6 months as a key biomarker of poor gut health contributing to chronic systemic inflammation and impaired growth.

#### Secondary outcomes

Biomarkers at ages 6 weeks and 3, 6 and 12 months
Plasma marker of chronic inflammation: (AGP; at 6 weeks and 3 and 12 months)Stool biomarker of intestinal inflammation: myeloperoxidaseStool biomarker of intestinal permeability: α1-antitrypsin (AAT)Plasma marker of acute inflammation: C-reactive protein (CRP)Plasma marker of gut mucosal integrity: intestinal fatty acid-binding protein (IFABP)Plasma growth hormones: insulin-like growth factor (IGF)-1 and its carrier protein IGF-binding protein 3Stool pH

Clinical outcomes to age 2 years
MortalityHospital admissionAll-cause sick-child clinic visitsDisease-specific sick-child clinic visits (e.g. diarrhoea; respiratory and skin infections)Anthropometric outcomes: weight, length, mid-upper arm circumference (MUAC), head circumference

Feeding and WASH practices and environmental factors that may influence the development of the gut microbiome will be assessed by questionnaires.

### Participant timeline {13}

Pregnant women and families will be provided with information about the study when attending ANC during the third trimester. Following the delivery of a live infant, newborns will be assessed by study staff according to the inclusion/exclusion criteria within the first 3 days after birth. After securing informed consent, newborns will be allocated randomly to one of the 4 study arms. Study staff will undertake a Ballard assessment to determine gestation, measure anthropometric indices and record infant feeding, WASH practices and environmental information using standardised questionnaires. Study staff will confirm that the infant has taken at least one breastfeed well and then assist the mother/carer in administering the first dose of the appropriate dietary supplement in infants allocated to the active study arms.

Study staff will visit daily for the following 9 days and then weekly to age 6 months to supervise the administration of the pro/synbiotic to infants in the intervention arms. The same visit schedule will be applied to infants in the control arm (no dietary supplement). At all visits, research staff will encourage exclusive breastfeeding and other positive health practices and facilitate transport to the clinic as required in unwell infants. Follow-up visits for all participants to collect data and stool and blood samples will be scheduled for 6 weeks, 3 months, 6 months and 12 months. A final follow-up visit at 2 years will be scheduled to record long-term outcomes (Fig. 1).

**Fig. 1 Fig1:**
[figure not shown]
PROSYNK study timeline

### Sample size {14}

A total of 600 newborns will be recruited. For the primary outcome, we predict raised AGP (> 1 g/L) in 35% infants at age 6 months in the control group [22]. The study requires a total of 524 infants (131 per am) to demonstrate a 50% reduction (relative risk = 0.50) in the prevalence of the primary outcome from 35% in the control arm to 17.5% in any of the intervention’s arms with 80% power and *α* = 0.0167. The alpha of 0.0167 is required to allow for three comparisons, one for each intervention arm, against the control arm. We will recruit 150 infants per group to allow for 13% dropouts.

We have used AGP concentration as a dichotomous outcome as a conservative approach as we wish to recruit sufficient numbers of children to compare other important biomarkers between groups. Using values of biomarkers as continuous variables will increase the power of the study to detect differences between the study arms. Using AGP as an example, we predict a mean log_10_ value of − 0.24 g/L in controls based on data from Zimbabwe [20]. In total, 102 infants in the intervention and the control group are required to show that mean AGP concentration is 20% lower in the intervention compared with the control group with 90% power at the 5% significance level.

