## Assignment of interventions: allocation

### Sequence generation {16a}

The trial statistician at LSTM, UK, will prepare computer-generated random allocation sequences using blocks of random size and stratified according to HIV exposure. The allocation ratio will be 1:1:1:1.

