## Statistical methods

### Statistical methods for primary and secondary outcomes {20a}

Demographic, clinical and laboratory data and also variables reflecting feeding, WASH practices and environmental factors will be summarised using simple descriptive statistics. Continuous variables will be summarised according to the number of subjects with non-missing data as mean, standard deviation, median, minimum and maximum. Categorical variables will be summarised according to the absolute frequency and percentage of subjects in each category level. The denominator for the percentages is the number of subjects with data available unless noted otherwise.

The primary outcome analysis will be based on the intention-to-treat (ITT) population which will include all randomised study subjects. The proportion of infants aged 6 months with abnormal AGP concentration (> 1 g/L) in each intervention arm will be compared with the proportion in the control arm. Data will be analysed using generalised linear models with treatment as the only predictor, AGP concentration at baseline as covariate, binomial distribution and log link function, generating the estimates of treatment effects in relative risk and their 95% confidence intervals (CI). Covariate-adjusted analysis will also be performed with covariates that affect the primary outcome (e.g. season of birth, HIV exposure, mode of delivery, mode of feeding, exposure to antibiotics, WASH and environmental factors such as water source, sanitation facilities, hygiene practices, use of soap, number of siblings, proximity to animals). Subgroup analysis will also be performed on the covariates used in the covariate-adjusted analysis.

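### Sizing the trial at 0.0167 is sound, but applying that level to all three final tests would be stricter than 5% family-wise control needs; Holm is a cheap improvement

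*Protocol article*

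**What the plan says.** The Protocol article, Sample size {14}, powers the trial for a fall in raised AGP at 6 months "from 35% in the control arm to 17.5% in any of the intervention’s arms with 80% power" and a per-comparison level of 0.0167. It justifies that level as follows: "The alpha of 0.0167 is required to allow for three comparisons, one for each intervention arm, against the control arm". The result is 131 infants per arm (524 in total), and then: "We will recruit 150 infants per group to allow for 13% dropouts".

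Under Statistical methods for primary and secondary outcomes {20a}, the proportion with raised AGP "in each intervention arm will be compared with the proportion in the control arm". Effects are reported as relative risks with 95% confidence intervals. That section names no multiplicity rule, neither a fixed level nor a step-down one. The 0.0167 in the sample-size section is the only level the article gives for handling the three primary comparisons.

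Who will be blinded {17a} says that the allocation sequence is provided to the study team only after the database for the primary outcome is locked and the statistical analysis plan is signed off.

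**The concern.** The word in "The alpha of 0.0167 is required to allow for three comparisons" that invites a second look is the claim of necessity. Three tests each at 0.05/3 are sufficient to hold the family-wise error at 5%, but using that level for every test is not necessary. After the smallest p-value has passed 0.05/3, only two hypotheses remain and 0.05/2 suffices for the next. After that passes, 0.05 suffices for the last.

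What is at stake is power for the second and third products. Several products working together is plausible here. Under Intervention description {11a} and Details of pro/synbiotics, arms 2 and 3 contain the same Lab4b bacteria, and arm 3 adds a prebiotic. If those bacteria reduce inflammation, both arms may well show it. A fixed 0.0167 carried into the final tests would then miss real effects more often than error control demands, and two similar products could look different because one narrowly missed a stricter threshold than was needed.

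**Working it through.** **Inputs from the article.** Control risk 35%; intervention risk 17.5%; difference 0.175; alpha 0.0167; power 80%; 131 analysable per arm; 1:1:1:1 allocation; three comparisons sharing one control. Sidedness is not stated; two-sided is assumed because it reproduces the stated number (one-sided gives 111 per arm).

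**Step 1: reproduce the planned number.** Two proportions, pooled variance under the null, no continuity correction:

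n = [z(1−α/2)·√(2·p̄·q̄) + z(power)·√(p₁q₁ + p₂q₂)]² / d²

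- p̄ = (0.35 + 0.175)/2 = 0.2625, so 2·p̄·q̄ = 2 × 0.2625 × 0.7375 = 0.3872, with root 0.6222
- p₁q₁ + p₂q₂ = 0.2275 + 0.1444 = 0.3719, with root 0.6098
- z for 0.0167 two-sided = 2.393; z for 80% power = 0.842
- n = (2.393 × 0.6222 + 0.842 × 0.6098)² / 0.175² = 130.9, so 131 per arm

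The article's figure is matched exactly.

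**Step 2: the level that planning needs under each rule.** Holm's first step is 0.05/3 = 0.0167. If only one product works, its test generally has to pass that first step. To secure 80% power in that case, a Holm trial is therefore sized at 0.0167 as well.

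**Step 3: power at 131 per arm.** Simulation of 500,000 trials per scenario, control risk 35%, risk 17.5% in each effective arm and 35% in each ineffective arm, shared control, two-sided pooled z-tests:

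| Products that work | Quantity | Fixed 0.0167 | Holm |
|---|---|---|---|
| One | Power for that product | 80.5% | 80.7% |
| Two | Power per effective product | 80.6% | 83.3% |
| Two | Both detected | 69.7% | 75.1% |
| Three | Power per product | 80.4% | 86.8% |
| Three | All three detected | 62.1% | 77.5% |
| Three | At least one detected | 95.0% | 95.0% |

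The gain per product is 80.7 − 80.5 = 0.2 points with one effective, 83.3 − 80.6 = 2.7 with two, and 86.8 − 80.4 = 6.4 with three. With unequal true risks of 17.5%, 21% and 24.5% (an assumed pattern), power by product goes from about 81%, 56% and 30% to about 83%, 63% and 42%.

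**Step 4: family-wise error.**

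| Products that work | Fixed 0.0167 | Holm |
|---|---|---|
| None | 4.55% | 4.55% |
| One | 3.18% | 4.18% |
| Two | 1.71% | 3.83% |

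The error is identical when nothing works. When some products work, Holm uses more of the allowance but stays below 5%. The shortfall from 5% under the global null comes mainly from the shared control. Holm does not recover it; a Dunnett-type rule does. Single-step Dunnett allows about 0.0189 per test, which would need 128 per arm instead of 131.

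**The case against.** The strongest reply is that the sentence on 0.0167 sits in the sample-size section and sets a planning level, which is right under either rule. This stands: neither the number of infants nor the planned 80% power is affected.

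Second, the analysis section does not commit the final tests to a fixed 0.0167, and the decision rule may be settled in a statistical analysis plan that is not shown. This also stands, so any loss of power is conditional on 0.0167 being carried forward to all three tests. What remains is that the article offers no other level for these comparisons and calls this one required, so a reader could easily apply it throughout. If each comparison were instead judged by its ordinary 95% interval, Holm would be stricter than that practice, not more powerful.

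Third, a fixed level is standard and comes with simple simultaneous intervals that match its tests. That is a real merit in general, but the article does not draw on it, because it reports plain 95% intervals and not 98.33% ones.

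Fourth, the largest gain, in detecting all three products, concerns a target the protocol does not set. It is powered for any one arm, and the chance of finding at least one effective product is the same under both rules. This is a fair limit on how much weight the 62% to 78% contrast can bear.

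**Conclusion.** The point holds as a cheap improvement. Used as the final level for all three products, 0.0167 is valid but more conservative than 5% family-wise control needs. At 131 per arm, Holm gains essentially nothing if one product works, about 3 points of power per product if two work, and about 6 points if all three work, within the same 5% bound.

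A reader might infer that 0.0167 is wrong, that the trial is wrongly sized, or that it gives up power for nothing. The documents do not support any of these. The sample size reproduces exactly and would be the same under Holm, no section fixes the final tests at 0.0167, and a fixed level has the advantage of simple matching intervals.

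The power figures assume two-sided unadjusted tests, the planned 35% and 17.5% risks, and 131 analysable infants per arm. The planned model with baseline AGP as covariate may shift the absolute values. Holm's 5% bound does not depend on these risks, provided each p-value is valid.

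**What to change.** Keep 131 analysable and 150 recruited per arm. In Sample size {14}, replace the statement that 0.0167 is required with one saying that the trial is sized at 0.0167 as the first step of a Holm procedure. In Statistical methods {20a}, and in the statistical analysis plan before it is signed off and the allocation is released, state that the three primary p-values are ordered and tested by Holm at 0.0167, 0.025 and 0.05, stopping at the first that fails, for a family-wise error of 5%. Step-down Dunnett is an acceptable alternative with slightly more power (87.4% against 86.8% per product when all three work).

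The cost is a sentence in each place and no extra infants. If simultaneous intervals (98.33% or Dunnett) are reported alongside, the interval for the second or third product may include 1 although Holm rejects. The text should therefore name the Holm test as the decision rule and the intervals as estimation.
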